### Sub-group analyses

Performance on measures at baseline (described above), as well as change in these measures over time, will be used to determine effects on CR treatment response. Additional measures not described above that will be included in sub-group analyses will be the Childhood Trauma Questionnaire (CTQ) [73], the State Trait Anxiety Inventory (STAI) [74], and a Demographic Questionnaire.

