### Randomisation

Randomisation to the group-based CR intervention, or not, will occur at 6 months. This time-point has been chosen to avoid differential early dropout based on randomisation and to provide a period of mood stabilising treatment prior to CR treatment. Computerised permuted block randomisation will be undertaken by the team’s biostatistician (CF) prior to the commencement of the study and will be stratified according to mood disorder type (BD or MDD). Sequentially numbered envelopes will be stored in a locked cabinet by an independent research coordinator and given to therapists after the 6-month research assessment. Each patient will be allocated a randomisation number which will not be re-allocated if the patient drops out of the study.

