At 6 months, patients will undergo a second objective cognitive and functional (University of California San Diego Performance Based Skills Assessment, Brief Version (UPSA-B) [58]) assessment (blind research assistant), a telephone interview (same measures as baseline), a psychiatrist review (same measures as baseline), and self-report questionnaires (described below). Immediately following this, patients will be randomised to the group-based CR intervention, or not. The CR intervention will be provided for an 8-week period, commenced between approximately 6 months and 9 months. At treatment-end (12 months) objective cognitive and functional assessment will be repeated, along with all research measures conducted at baseline. Qualitative interviews and treatment satisfaction questionnaires will be completed at 12-months only by a research nurse trained in qualitative methodology. The same measures conducted at the 6-month time-point will be conducted at 18-months (with the exception of the UPSA-B), and at 24 months, three measures will be conducted via telephone (LIFE, FAST, MARS). Schedule of enrolments, assessments and interventions is presented in Table 1 and a populated SPIRIT checklist is provided in Additional file 1.

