### Primary outcome

The outcome measures for the trial align with ISBD Targeting Cognition Taskforce recommendations for CR trials in BD [5]. A single composite score (Global Cognition) representing overall cognitive performance at each cognitive assessment (baseline, 6 months, 12 months, 18 months) will be calculated. Change in Global Cognition from 6 months (before randomisation to group-CR) to treatment-end (12 months) will be the primary outcome measure.

Cognitive function will be assessed with a battery of cognitive tasks designed to assess verbal learning and memory, visuospatial learning and memory, sustained attention, working memory, executive functioning, psychomotor speed and social cognition. These cognitive domains are included based on recommendations from the ISBD Targeting Cognition Taskforce [5], as well as research showing these domains to be significantly impaired in acutely-unwell patients with mood disorders [6, 59] and to be sensitive to the effects of Cognitive Remediation interventions [60]. The cognitive assessment will include the following tests:Rey Auditory-Verbal Learning Task [61]Brief Visuospatial Memory Test – Revised [62]Digit Span Forwards and Backwards [63]Trail Making Test – Part A and B [64]Delis-Kaplan Executive Function System—Fluency Battery (Category Fluency, Category Switching) [64]Digit Symbol Coding [63]Continuous Performance Test [62]Stroop Task [64]Negative Affective Priming Task [65]Reading the Mind in the Eyes Test [66]Facial Expression Recognition Test [67]

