#### Power

This study is powered on the cognitive outcomes demonstrated in our preliminary RCT of Metacognitive Therapy versus Cognitive Behavioural Therapy for outpatients with MDD [16]. Metacognitive Therapy includes a simple cognitive training intervention (Attention Training Technique). A positive effect size difference between Metacognitive Therapy and Cognitive Behavioural Therapy was found on measures of visuospatial learning and attention (0.6) [16]. To detect a similar effect size for Global Cognition as statistically significant (2-tailed α = 0.05), 45 patients per group would be necessary for 80% power. We aim to recruit 50 patients per group. All statistical tests will utilise a 2-tailed *p*-value of < 0.05 to indicate statistical significance.

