### Exploratory outcomes

Change in the following measures between treatment arms will be assessed as exploratory outcomes (see Table 1 for time-points of administration).Quick Inventory for Depressive Symptomatology – Self Report, QIDS-SR [52], as a measure of self-reported depression symptoms.Quality of Life in Bipolar Disorder (QoL-BD) [68]), a validated measure of quality of life for those with BD.Biological Rhythms Interview of Assessment in Neuropsychiatry (BRIAN) [69] to assess biological and sleep rhythms.Ruminative Responses Scale from the Response Style Questionnaire (RRS) [70], a measure of participants’ tendency to ruminate.Metacognitions Questionnaire – Short-form (MCQ-30 [71]) to assess individuals’ beliefs about their thinking processes.Eysenck Personality Questionnaire – Brief Version (EPQ-BV) [72] will assess individuals’ level of neuroticism and extraversion.MARS [56] will assess medication adherence in an interviewer-administered format.Biological measures: change in levels of inflammatory markers (including C-reactive protein levels (CRP) and key cytokines), androgens (Free Testosterone, Total Testosterone, Free Androgen Index, Sex Hormone Binding Globulin, Luteinizing Hormone, Follicle Stimulating Hormone Prolactin – females only), and Vitamin C will be analysed from blood samples.

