#### Analysis of sub-group effects

Sub-group analyses will use general linear models, and will include sub-group measures and the interaction between treatment arm and these measures. Interaction terms will be used to evaluate the differential effects of CR treatment dependent upon the level of the baseline and change features.

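### Sub-group models allow change measured after randomisation to act as a modifier of the CR effect, which does not estimate effect modification

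*Protocol article*

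**What the plan says.** The Sub-group analyses section names two kinds of candidate modifier. One is performance on the trial measures at baseline. The other is their later course: "as well as change in these measures over time, will be used to determine effects on CR treatment response". The next section, Analysis of sub-group effects, puts both into the model: "Interaction terms will be used to evaluate the differential effects of CR treatment dependent upon the level of the baseline and change features".

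The timing is fixed elsewhere in the article:

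- Randomisation: "Randomisation to the group-based CR intervention, or not, will occur at 6 months". The allocation envelope goes to the therapist after the 6-month research assessment.
- Primary outcome: "Change in Global Cognition from 6 months (before randomisation to group-CR) to treatment-end (12 months) will be the primary outcome measure".
- Procedure: "At treatment-end (12 months) objective cognitive and functional assessment will be repeated, along with all research measures conducted at baseline". Most measures are collected again at 18 months, and three at 24 months.

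Many of these measures are also outcomes. The Exploratory outcomes section says: "Change in the following measures between treatment arms will be assessed as exploratory outcomes". Its list includes self-rated depression, rumination, metacognition and medication adherence. The secondary hypotheses expect functioning and mood to improve more with CR.

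The abstract describes the sub-group analyses as assessing baseline features only and does not mention change.

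**The concern.** An effect modifier has to be a characteristic that allocation cannot influence. If CR can alter the variable, patients with the same value of it in the two arms are no longer comparable groups, and randomisation does not protect the comparison within levels of it. The interaction then mixes mediation (the measure moved and carried the outcome with it), reverse causation (patients who gained cognitively rate themselves better) and selection.

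The purpose is practical. The Background says that factors influencing response to CR are sought so that the intervention can be tailored to individuals. A clinician choosing whether to offer CR knows only what is measured before it starts. Change between months 6 and 12 could not inform that choice even if its interaction were estimated without error. At worst, the paper would report that CR works better in patients whose mood or self-rated cognition improved, and readers would take this as a selection rule when it describes what happened during treatment.

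**Working it through.** **1. Which changes precede allocation.** From Randomisation, Procedure and Primary outcome:

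| Change window | Position relative to month-6 randomisation | Can CR affect it? |
|---|---|---|
| 0 to 6 months | before | no |
| 6 to 12 months | after; same window as the primary outcome | yes |
| 0 to 12 months | straddles | yes |
| 12 to 18, 18 to 24 months | after | yes |

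The two sub-group sections admit every row. Only the first is a valid modifier.

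**2. Inputs.** From the Power section: effect 0.6 SD, two-sided 0.05, 50 per arm. The plan's own sample size reproduces: the two-sample t-test needs 44.6, so 45 per group for 80% power. That figure is not in dispute and supplies only the effect size used here. Everything else below is assumed, because the article gives no figures for how these measures relate to cognitive change.

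**3. False interaction through reverse causation.** Let Y be the 6-to-12-month outcome change and A the arm. Let Y = 0.6A + e with SD 1, so that CR helps everyone equally. Let the measure's change follow the outcome: M = s·Y + noise (SD 1), with slope s₁ in the CR arm and s₀ in the control arm. Regressing Y on A, M and A×M, the slope of Y on M within an arm is s/(1 + s²), so the interaction has expectation

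s₁/(1 + s₁²) − s₀/(1 + s₀²).

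For s₁ = 0.5 and s₀ = 0 this is 0.5/1.25 − 0 = 0.40. The variance of M is 1.25 and 1. The residual variance of Y is 0.8 and 1 (pooled 0.9). The standard error is therefore about √(0.9/(50×1.25) + 0.9/50) = √(0.0144 + 0.0180) = 0.18, and 0.40/0.18 = 2.2. That exceeds 1.96 in about 60% of trials by the normal approximation and in 57-58% by simulation. Other slopes, by simulation:

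| Slope, CR / control (assumed) | Interaction significant at 0.05 |
|---|---|
| 0.5 / 0.5 | 5% |
| 0.5 / 0.4 | 6% |
| 0.1 / 0 | 8% |
| 0.5 / 0.25 | 15-16% |
| 0.2 / 0 | 16% |
| 0.5 / 0 | 57-58% |

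**4. Uniform shift or shared cause.** If CR moves M by the same amount in everyone and M is simply correlated with Y, the interaction test keeps its level (about 5%). The arm term does not survive: its expectation is the true effect minus correlation × shift in M. With a shared cause loading 0.7 on each (correlation 0.7 × 0.7 = 0.49) and a shift of 0.5 SD, this is 0.60 − 0.49 × 0.5 = 0.355. Simulation gives 0.35.

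**5. Unequal uptake.** Suppose patients differ in how much they take from CR, in a way unrelated to anything measured before randomisation, and that this moves both M and Y (mean shift 0.6 SD in each, residual correlation 0.3, all assumed). The interaction with post-randomisation change is then significant in 5.6%, 10.8%, 21.7% and 45.4% of trials for uptake SDs of 0.3, 0.5, 0.7 and 1.0. In the same simulations the interaction with pre-randomisation change stays at 4.7% to 5.0%.

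**The case against.** The strongest reply is that the text leaves a window open and does not commit to a wrong one. Everyone receives six months of IPSRT before randomisation, so month-0 to month-6 change is a natural and legitimate modifier here. The abstract speaks of baseline features, and a condensed article may leave the exact window to a fuller document. This stands in part. A reader might infer that the trial definitely intends to use 6-to-12-month change; the article does not say so. But change over time, in a schedule running to 24 months, literally includes later change, and no sentence excludes it. As worded, the rule permits an invalid analysis and disagrees with the abstract.

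Four other inferences go too far:

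- **That the main result is compromised.** The primary and secondary models contain only arm and stratum. The attenuated arm term arises only inside the sub-group models, where the article relies on the interaction terms.
- **That 58% is the expected error rate.** It needs self-rating to follow cognitive gain with CR and not at all without it. Nothing in the article supports that contrast, and with equal slopes there is no inflation.
- **That month-0 values are the wrong baseline.** They precede randomisation and are valid modifiers, and the Background gives a reason for interest in baseline cognition. The 6-month value is a sensible addition, and the month-0 value need not be replaced.
- **That multiplicity is an error here.** The Power section does apply one threshold throughout ("All statistical tests will utilise a 2-tailed" p-value below 0.05), but the article gives no count of moderators, related scales are not independent, and the Background describes these factors as belonging to secondary and exploratory analyses.

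**Conclusion.** The point holds in limited form and should be fixed. The two sub-group sections allow variables that CR can change, and that the trial itself analyses as outcomes of CR, to be used as modifiers of CR. An interaction with such a variable does not estimate effect modification, whatever its false-positive rate, and cannot serve the stated aim of tailoring.

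The numerical harm is uncertain. With a uniform 0.6 SD effect and 100 patients, false interactions run from about 5% to 58%, with about 15-16% at intermediate assumed slopes. The arm term in the same model can fall from 0.60 to about 0.35 under the assumed shared cause. These figures rest on assumed slopes, loadings and complete data. The conclusion about interpretation does not depend on them: it follows from month-6 randomisation and the assessment schedule.

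**What to change.** In Sub-group analyses and Analysis of sub-group effects, limit effect modifiers to values fixed before randomisation: the month-0 value, the 6-month value, and the change from month 0 to month 6. State that any analysis involving change after month 6 will be reported separately as exploratory mediation or association, and not as moderation of CR response. Align the abstract with the two sections, so that all three name the same set of modifiers.

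The cost is wording only. For measures taken at month 0 and month 6, the pre-randomisation values are already on the schedule, and neither sample size nor procedures change. The one loss is that post-randomisation change can no longer be presented as a moderator. The change should be made before outcome data are analysed.

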#### Analysis of sub-group effects

Sub-group analyses will use general linear models, and will include sub-group measures and the interaction between treatment arm and these measures. Interaction terms will be used to evaluate the differential effects of CR treatment dependent upon the level of the baseline and change features.

### Qualitative interview

A semi-structured qualitative interview will be conducted at treatment-end (12 months) by a trained research nurse. Interviews will focus on the patients’ experience of their mood disorder, particularly on their cognitive and everyday functioning. Patients will also be asked about their experience of treatment and how they feel it impacted on their mood disorder symptoms. Qualitative data will be analysed using thematic analysis, as per Crowe et al. [41].

### Treatment satisfaction

Two scales developed by study investigators will be used to assess satisfaction and acceptability of IPSRT and CR components of treatment at the 12-month time-point. These scales measure responses on Likert-type scales, as well as providing space for comments from participants.

### Adverse events

Serious adverse events will be assessed using a Serious Adverse Events Questionnaire (as per [75]) at 6 and 12 months.

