## Background

The spectrum of mood disorders includes Major Depressive Disorder (MDD) and Bipolar Disorder (BD). Mood disorders are highly recurrent, long-term conditions, and are among the leading causes of disability worldwide [1, 2]. In New Zealand, high prevalence and disability associated with mood disorders applies to all ethnic groups and causes significant interference with functioning and suffering [3]. Rates of relapse in BD for those receiving routine care (medication alone) are 43% within 12 months, 57% within 2 years, and 77% within 4 years [4]. In Christchurch (New Zealand), where care consists mainly of medication and case management, 40% of patients admitted to a Specialist Mental Health Service (SMHS) with a mood disorder were readmitted into a SMHS within a year of discharge (data from Canterbury District Health Board SMHS). Reducing relapse and achieving longer duration between episodes is important because sustained periods of recovery of between 1 and 3 years are associated with progressively lower future relapse [4]. It is thus vital for treatment research in mood disorders to examine interventions that can be used alongside medication in order to promote long-term recovery.

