### Development of the current trial

We have recently completed a pragmatic RCT [30] which examined a novel combination of CR, IPSRT and medication management for people with mood disorders. Individuals (*n* = 68) recently discharged from SMHS in Christchurch, New Zealand, were recruited into the trial and randomised to receive a 12-month course of IPSRT either with (IPSRT-CR) or without CR (IPSRT alone). For those randomised to IPSRT-CR, CR was incorporated into the 50-min therapy sessions from an early stage of treatment and continued for 12 sessions. However, the addition of CR to IPSRT did not significantly improve the primary outcome, Global Cognition, more than IPSRT alone. On the other hand, significantly greater improvement in psychosocial functioning and longitudinal depression symptoms was evident in the IPSRT group compared with the IPSRT-CR over the treatment period. During the trial, therapists had concerns about integrating CR into IPSRT at such an early stage of treatment. At study intake, 43% of the sample were ‘in episode’, and thus, therapists often prioritised stabilisation of mood over CR. This was a factor contributing to the comparatively low dose of CR (average of 7 h) provided in our trial compared with other recent RCTs of CR in BD [21, 22]. We therefore propose a follow-on RCT which will once again aim to optimise psychological treatment to improve cognitive function, and thereby, to improve functioning and mood outcomes in individuals with mood disorders. However, the CR component will, in this trial, be conducted at a later stage of treatment and will be delivered separately from ongoing IPSRT. For the first 6 months of the 12-month intervention period, all individuals will receive the same intervention; individual IPSRT. At 6 months, individuals will be randomised to receive additional group-based CR (8 sessions over 8 weeks) or no additional treatment. Shifting to a group approach should allow for a higher and more consistent dose of CR to be delivered, and at a point when individuals should have a more stable mood.

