
CR treatment will occur in the final 6 months of each patient’s treatment, and will be commenced between approximately months 6 to 9 depending on patient numbers (see Discussion for rationale).

There will be 3 to 5 patients in each group, and two therapists. The trial lead, KD (Clinical Psychologist), received in-person training in ABCR in June 2019 from [name] and his lab members, and KD has trained all ABCR-NZ group therapists (4 mental health nurses, 1 psychiatrist) for the current protocol.

With regards to fidelity of both IPSRT and group-CR interventions, therapy sessions will be audio-taped and 10% randomly selected and rated to ensure adherence to IPSRT and CR therapy protocols using checklists for key components of each therapy (as in Douglas et al. [30]). Therapists participate in fortnightly group supervision, led by therapists with extensive experience in training and delivery of IPSRT (MI) and CR (KD).

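### Serious adverse events have one scheduled collection after randomisation, at month 12, while functioning and mood benefit is hypothesised to month 24

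*Protocol article*

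**What the plan says.** The Adverse events section consists of one sentence: "Serious adverse events will be assessed using a Serious Adverse Events Questionnaire (as per [75]) at 6 and 12 months". The article describes no other source of serious-event data.

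On the timing of allocation, the Randomisation section says "Randomisation to the group-based CR intervention, or not, will occur at 6 months". The Procedure section, having listed the 6-month assessments, adds "Immediately following this, patients will be randomised to the group-based CR intervention, or not".

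On exposure, Procedure says "The CR intervention will be provided for an 8-week period, commenced between approximately 6 months and 9 months". IPSRT runs for 12 months in both arms.

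On follow-up, the secondary hypotheses expect general and psychosocial functioning to improve more with IPSRT-CR at treatment-end, 18 and 24 months, and mood symptoms to improve more at treatment-end and the follow-up time-points. The Secondary outcomes section takes FAST and LIFE to month 24. Procedure limits the 24-month contact to a telephone call with LIFE, FAST and MARS.

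On the 18-month assessment, Procedure says "The same measures conducted at the 6-month time-point will be conducted at 18-months (with the exception of the UPSA-B", with no other exception named.

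**The concern.** A questionnaire at 6 and 12 months looks like two safety assessments. In this design the first comes before allocation, so it cannot inform a comparison of IPSRT-CR with IPSRT alone. One scheduled form remains, and it closes at treatment-end, whereas the benefit hypotheses run for a further year.

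If the trial reports durable benefit to month 24, a reader will want serious events over the same span. Under the stated schedule, a difference between arms in serious events in months 12 to 24 would have no scheduled route into the data. Such a difference is not far-fetched here. In the team's previous trial, "significantly greater improvement in psychosocial functioning and longitudinal depression symptoms was evident in the IPSRT group compared with the IPSRT-CR". That concerns smaller improvement, not serious events, but it is a reason to look at both directions of effect for as long as benefit is assessed.

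**Working it through.** The plan gives no figure for safety coverage, so there is none to reproduce. The check sets the stated schedules side by side.

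**Inputs**
- Randomisation: month 6, after the 6-month assessment (Randomisation; Procedure).
- Serious-event questionnaire: months 6 and 12 (Adverse events).
- Last follow-up: month 24 (Procedure).
- CR: 8 weeks, starting between about months 6 and 9 (Group-based cognitive remediation; Procedure).

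**Step 1. Forms that can compare the arms.** The month-6 form is pre-randomisation. Of the three post-randomisation assessments (months 12, 18 and 24), one has the questionnaire.

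**Step 2. Share of follow-up covered.**
- Post-randomisation follow-up: 24 − 6 = 18 months.
- Covered by the 12-month form, if it recalls back to month 6: 12 − 6 = 6 months, and 6/18 = 33%.
- No scheduled collection: 24 − 12 = 12 months, and 12/18 = 67%.

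**Step 3. Does the 12-month form reach the end of CR?** Eight weeks is about 1.84 months.
- Start at month 6: CR ends at about 6 + 1.84 = 7.84, leaving 12 − 7.84 = 4.16 months (about 18 weeks) before the form.
- Start at month 9: CR ends at about 9 + 1.84 = 10.84, leaving 12 − 10.84 = 1.16 months (about 5 weeks).

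So the form can span all of CR in either case. The gap lies after treatment, not during it.

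**Step 4. The 18-month sentence.** If the questionnaire counts among the 6-month measures, the Procedure sentence repeats it at 18 months. Coverage would then be 18 − 6 = 12 of 18 months (67%), leaving 6 of 18 (33%) open. The Adverse events section, which is the specific statement, names only 6 and 12 months. The Procedure sentence is also inexact elsewhere: QIDS-C and YMRS are given at 6 months, yet the Mood symptoms section stops them at 12. The specific section therefore probably governs, but the two do not agree as written.

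**Step 5. Month 24.** Procedure restricts this call to LIFE, FAST and MARS. The questionnaire is absent on either reading of Step 4.

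**Step 6. What the other instruments record.** LIFE is described as recording episodes and sub-syndromal symptoms of depression, hypomania and mania over the preceding 6 months. FAST records functioning. Neither description mentions deaths, admissions, self-harm or other serious events.

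**The case against.** The strongest reply is that the window fits the treatment. Both interventions end by month 12, so the 12-month form can cover the whole randomised treatment period, and collecting serious events only during a behavioural add-on of modest intensity is a defensible choice. This stands, subject to a recall period that the article does not give. It does not answer the mismatch with hypotheses that extend to month 24.

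A second reply is that harm is observed after month 12, because LIFE and FAST run to month 24 in both arms and SAS to 18 months. This also stands for mood episodes and functioning, the kind of deficit seen in the previous trial. It would be wrong to say that relapse goes unobserved in the second year. What remains uncollected is the serious event as such.

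Two stronger readings are tempting, and the documents do not support them.

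- **That most serious events will be missed.** A reader might project this from the Background statement that 40% of patients "were readmitted into a SMHS within a year of discharge". That figure counts return to a specialist service, which is not stated to mean an inpatient stay and cannot be equated with a serious adverse event. It runs from discharge, whereas entry may come up to 3 months later. A constant-rate projection also conflicts with the bipolar relapse figures in the same section: 43% by 12 months and 57% by 2 years imply yearly hazards of −ln(0.57) = 0.56 and then −ln(0.43/0.57) = 0.28. The 67% above is a share of time, not of events.
- **That nothing is recorded for someone who dies, is in hospital or has left before month 12.** Spontaneous or expedited reporting and the handling of absentees commonly sit in the full protocol, which is not shown. A data safety and monitoring committee also meets every 6 months. The article's silence is not evidence of absence.

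**Conclusion.** The point holds as a limited one. On the stated schedule, one of three post-randomisation assessments collects serious events, and 12 of 18 post-randomisation months (67%) have no scheduled collection. If the Procedure sentence is taken literally for month 18, the open period falls to 6 of 18 months (33%), and month 24 remains without collection.

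This rests on three assumptions: that the Adverse events section states the whole questionnaire schedule, that the 12-month form recalls back to month 6, and that no other planned source supplies serious events after month 12. The content of Table 1 was not available to check the first.

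The consequence is that benefit and serious harm would be reported over different periods. The primary analysis and power are not affected. This is a cheap improvement, not a defect in the main comparison.

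**What to change.** - Amend the Adverse events section so that the existing questionnaire is also given at the 18-month assessment and in the 24-month telephone call, each time covering the period since the last contact.
- Bring the Procedure section into line: state whether the questionnaire belongs to the 18-month set, and add it to the 24-month list. Correct the same sentence for QIDS-C and YMRS.
- Report the 6-month form as pre-randomisation data.
- Compare the arms on serious events from randomisation to month 24.

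The cost is a few minutes at two contacts that already take place. A change to data collection also goes to the ethics committees and onto the registry record under the Protocol modification section. No new visits are needed.
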